### Sample size

This is a superiority study. Based on pilot case observations and expert feedback, the major indicator Chao1 index (α-diversity) at week 12 is expected to differ by 145 between the two groups, with a standard deviation of 230 [25]. Assuming *α* = 0.025 and *β* = 0.20, we calculated that the sample size should be at least 47.9 in each group [26]. If the lost-to-follow-up rate is no more than 20%, the sample size should be at least 57.5 in each group. Moreover, Shannon’s index (α-diversity) of the primary measure at week 12 is expected to differ by 0.9 between the two groups, with a standard deviation of 0.8. Thus, the sample size should be at least 15.0 in each group. If the lost-to-follow-up rate is no greater than 20%, the sample size should be at least 18.0 in each group. The larger value (57.5) is used as the calculated sample size. Based on the above assumptions and our budget, we will recruit a total of 120 participants for this study, with 60 participants in each group.

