### Primary outcome

Based on faeces, the GM from day 0 (week 0), day 28 (week 4), day 56 (week 8), and day 84 (week 12) will be evaluated. For the GM assessment, DNA will be extracted from the stool samples with the QIAamp Fast DNA Stool Mini Kit (Qiagen, Hilden, Germany) following the manufacturer’s instructions, and the DNA quality will be examined by agarose gel electrophoresis and a Nanodrop spectrophotometer. Shotgun metagenomic sequencing will be performed on all samples by using an Illumina HiSeq 2500 instrument. Libraries will be constructed from DNA fragments ~ 300 bp in length and paired-end reads will be generated by sequencing 150-bp lengths in the forward and reverse directions. Meanwhile, the metagenomic analysis will include several components: the analysis of alpha and beta diversities in each group to understand whether the differences in the microbiota compositions of groups are significant, as well as the taxonomic characteristics of the study and control groups at the phylum, genus, and species levels to identify specific genes related to the individual differences in GERD. Metagenomic biological pathway analysis will be used to evaluate the effect of probiotics on the function of gut metagenomics in patients with GERD and, hopefully, to explore the metagenomic biological pathways contributing to the mechanism of probiotics in the treatment of GERD.

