### Statistical analysis

First, the intention-to-treat (ITT) analysis will be conducted between the two groups, including all the intended participants who do or do not complete the follow-up. Then, per-protocol (PP) analysis will be conducted in the four-subgroup datasets according to compliance (100%, ≥ 80%, 60–80%, and < 60%) to validate the robustness of the results. The datasets will be analysed as described below.

With a randomized block design, the nonparametric rank sum test and Friedman M test will be performed to analyse the difference in each outcome measure at each time point (see “Intervention Outcome Measures” for details) between the two groups, including the GM analysis, RDQ score, GSRS score, faecal metabolomics, and BMI. The significance level will be set to *P* = 0.05. Next, the paired Wilcoxon signed-rank test will be performed for pairwise intragroup comparisons to analyse the change trends for each outcome measure before, during, and after the probiotic intervention. The significance level will be set at *P* = 0.05/[k(k-1)/2], where k is the number of groups in the comparison. For analysis of the oesophagitis grade, the diagnosis of LA-B at baseline and LA-A at week 12 indicates that the patient's oesophagitis grade will have decreased by one level. If the grade is LA-C at baseline and LA-A at 12 weeks, the patient’s oesophagitis grade will have decreased by 2 levels. The number of oesophagitis grades reduced by 1 and 2 levels in each group will be calculated. Then, a chi-square (*χ*^2^) test will be performed. AE rates in the two groups will be compared by the *χ*^2^ test or Fisher’s exact probability test based on the occurrence frequency of AE, and the difference in treatment compliance will be also examined by the *χ*^2^ test.

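### The trial is sized at two-sided alpha 0.025 on Chao1 and Shannon at week 12, but the analysis section sets 0.05 for between-group tests of every measure at every visit and names no primary test

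*Protocol article*

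**What the plan says.** **Sample size section.** It opens with "This is a superiority study". The planning values are "Assuming *α* = 0.025 and *β* = 0.20"; sidedness is not given. Chao1, called the major indicator, "at week 12 is expected to differ by 145 between the two groups, with a standard deviation of 230", and for it "we calculated that the sample size should be at least 47.9 in each group". Shannon's index "at week 12 is expected to differ by 0.9 between the two groups, with a standard deviation of 0.8", followed by "Thus, the sample size should be at least 15.0 in each group". The larger requirement is kept, and 60 per group are to be recruited.

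**Primary outcome section.** The primary outcome is the gut microbiome at weeks 0, 4, 8 and 12. It covers "the analysis of alpha and beta diversities in each group to understand whether the differences in the microbiota compositions of groups are significant", plus taxonomy at three levels and pathway analysis. No index or visit is singled out.

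**Statistical analysis section.** Rank-sum and Friedman tests compare the two groups on each outcome, microbiome included, at each time point. For these, "The significance level will be set to" P = 0.05. One adjusted level is printed, 0.05/[k(k-1)/2], and it is attached to the paired Wilcoxon comparisons within groups.

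**The concern.** A superiority claim rests on a between-group test. Here the test that determined the sample size (Chao1, with Shannon, at week 12, alpha 0.025) appears in neither the outcome section nor the analysis section. What appears there is a wide family of between-group comparisons at 0.05. A reader of the final report could not tell which result was meant to decide the trial, or at what level.

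The gap also has a consequence inside the protocol. Under footnote 11 of Table 1, the faecal metabolomics assay depends on a significant probiotic effect on the microbiome being found, yet no section says which index, visit or alpha decides that.

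**Working it through.** **Inputs (Sample size section).** Chao1: difference 145, SD 230. Shannon: difference 0.9, SD 0.8. Alpha 0.025, beta 0.20, equal groups.

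**1. Reproduce the stated sizes.** Normal approximation, per group: n = 2 (z_a + z_b)² (SD/difference)², with z_b = 0.842.

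| Reading of alpha | z_a | Chao1 | Shannon |
|---|---|---|---|
| Two-sided 0.025 | 2.241 | 2 × 3.083² × (230/145)² = 47.83 | 2 × 3.083² × (0.8/0.9)² = 15.02 |
| One-sided 0.025 (= two-sided 0.05) | 1.960 | 2 × 2.802² × (230/145)² = 39.50 | 2 × 2.802² × (0.8/0.9)² = 12.40 |
| Stated | | 47.9 | 15.0 |

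Rounding the Chao1 effect size 145/230 = 0.6304 to 0.63 gives 47.90 exactly. So 0.025 was used as a two-sided level and is not one tail of a two-sided 0.05 test. A rank-test allowance does not rescue the 0.05 reading either: 39.5/0.955 = 41.4.

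**2. Compare with the analysis level.** The between-group level is 0.05. The adjusted level covers only comparisons within groups; if k is the four time points it is 0.05/6 = 0.0083. No printed rule brings the between-group tests to 0.025.

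**3. Error rate under an assumed either-one-succeeds rule.** The protocol states no such rule; this shows what the open wording would allow.

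- Two indices at week 12, each at 0.05, independent: 1 − 0.95² = 9.75%. By simulation (400,000 draws), about 9.0% at an assumed correlation of 0.5 and 7.8% at 0.8.
- Two indices at three post-baseline visits, six independent tests: 1 − 0.95⁶ = 26.5%. With an assumed between-visit correlation of 0.5, about 19% to 24% for between-index correlations from 0.8 down to 0.
- Two indices at week 12, each at 0.025: at most 2 × 0.025 = 5%, whatever the correlation.

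**4. Chao1 power with 48 completers per arm** (60 × 0.8 = 48).

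| Method | Two-sided 0.025 | Two-sided 0.05 |
|---|---|---|
| Normal approximation | 80% | 87% |
| t-test | 79% | 86% |
| Rank-sum (normal data, relative efficiency 0.955) | 77% | 85% |

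The rank-sum row applies the t-test calculation to 48 × 0.955 = 45.8 per arm. A simulation of the rank-sum test itself (20,000 draws, normal data) gives 77% and 85%.

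**The case against.** The strongest reply is that only the 0.025 against 0.05 mismatch is stated, and the rest is read in. Much of this stands.

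- **Alpha split.** A reader might infer that 0.05 was divided over two indices. The arithmetic fits that, but the protocol does not say so. It could equally have one lead endpoint (Chao1) with Shannon as a supporting check, or two endpoints that must both succeed. Under either, testing at 0.05 would not inflate the week-12 error rate and the sizing would simply be conservative.
- **Success rule.** A reader might infer that any microbiome result below 0.05 makes the trial positive. No section says this, so the percentages in step 3 are conditional.
- **Power.** Moving from 0.025 to 0.05 raises power, so the mismatch does not leave the trial underpowered.
- **Scope of the primary outcome.** Pathway analysis is worded partly as exploration, so not every listed component should be read as confirmatory.
- **Analysis plan.** Testing order and the handling of omics families are commonly left to a plan that is not shown here.

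The reply does not remove the core. The protocol itself fixes both alphas, and they differ. It also defines the primary outcome in its own section, without the index and visit used for sizing. These are conflicts in printed text, not omissions.

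**Conclusion.** The concern holds as an inconsistency. The sizing used two-sided 0.025 for Chao1 and Shannon at week 12; the analysis uses 0.05 for between-group tests of every measure at every visit; and the primary between-group comparison is not named where it must be. The first part rests on arithmetic that matches both stated figures.

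The effect on the error rate depends on a success rule that the protocol leaves open. It is nil at week 12 if Chao1 alone decides or if both indices must succeed. It is up to 9.8% if either index suffices at week 12, and up to 26.5% if either suffices at any post-baseline visit. The upper values assume independent tests. The documents do not support a claim that the false-positive rate is already at these levels.

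**What to change.** 1. In the Primary outcome and Statistical analysis sections, name the week-12 between-arm comparisons of Chao1 and Shannon as the primary tests, each at two-sided 0.025 as sized. Alternatively, if Chao1 alone is the lead endpoint, name it alone, make Shannon supportive, and state one alpha in both the Sample size and Statistical analysis sections.
2. Label beta diversity, taxa, pathways and the other visits as secondary or exploratory.
3. State in the Sample size section that alpha 0.025 is two-sided and whether it applies per index.
4. State the Chao1 power for the planned rank-sum test.

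The change is wording only and should be made before unblinding. It needs no extra patients: 47.83/0.8 = 59.8, within the planned 60 per group. The cost is a stricter threshold than 0.05. At 48 completers per arm, power at 0.025 is 80% only by the normal approximation; it is about 79% by t-test and about 77% by rank-sum test on normal data, slightly below the planned 80%.

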### Data collection and collation

All study participants will be assigned a study ID. Electronic data will be stored in a secure password-protected database. All paper data collected will be stored at the site, and only the study team will have access to the data. The study results will be independently analysed at the end of the study. No interim analysis is planned. The GM and metabolomics data detected from stool samples will be analysed by the Key Laboratory of Dairy Biotechnology and Engineering, Ministry of Education. All records that contain names or other personal identifiers referring to a specific volunteer, such as ID number and informed consent forms, will be stored separately from the study records. The database will be password protected by the data management team (DMT).

### Statistical analysis

First, the intention-to-treat (ITT) analysis will be conducted between the two groups, including all the intended participants who do or do not complete the follow-up. Then, per-protocol (PP) analysis will be conducted in the four-subgroup datasets according to compliance (100%, ≥ 80%, 60–80%, and < 60%) to validate the robustness of the results. The datasets will be analysed as described below.

With a randomized block design, the nonparametric rank sum test and Friedman M test will be performed to analyse the difference in each outcome measure at each time point (see “Intervention Outcome Measures” for details) between the two groups, including the GM analysis, RDQ score, GSRS score, faecal metabolomics, and BMI. The significance level will be set to *P* = 0.05. Next, the paired Wilcoxon signed-rank test will be performed for pairwise intragroup comparisons to analyse the change trends for each outcome measure before, during, and after the probiotic intervention. The significance level will be set at *P* = 0.05/[k(k-1)/2], where k is the number of groups in the comparison. For analysis of the oesophagitis grade, the diagnosis of LA-B at baseline and LA-A at week 12 indicates that the patient's oesophagitis grade will have decreased by one level. If the grade is LA-C at baseline and LA-A at 12 weeks, the patient’s oesophagitis grade will have decreased by 2 levels. The number of oesophagitis grades reduced by 1 and 2 levels in each group will be calculated. Then, a chi-square (*χ*^2^) test will be performed. AE rates in the two groups will be compared by the *χ*^2^ test or Fisher’s exact probability test based on the occurrence frequency of AE, and the difference in treatment compliance will be also examined by the *χ*^2^ test.

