### Volunteer recruitment

Posters will be disseminated at the hospital to recruit participants. During their appointment at the Department of Gastroenterology in the First Affiliated Hospital of Nanchang University, volunteers who are interested in the study will undergo preliminary evaluations based on the inclusion and exclusion criteria. Additionally, the investigator will explain the purpose, process, and potential benefits and risks of this study, and the volunteers may choose to participate by signing the informed consent form. Next, the volunteers will undergo further screening to determine their eligibility. Eligible participants will receive the study intervention and follow-up. The following steps describe the formal intervention and follow-ups (Table 1).

**Table 1 Tab1:** Study and follow-up schedule

Item^1,10^		Screening	Baseline	Initial treatment		Maintenance treatment
		Visit 0	Visit 1	Visit 2	Visit 3	Visit 4
		Days −3 to 0	Day 0	Week 4	Week 8	Week 12
Basic demographics		X				
Vital signs, physical examination		X				
Allergies, medical history^2^, medication history^3^, surgical history^4^		X				
Smoking and drinking		X				
Gastroscopy		X^5^				X^6^
Abdominal ultrasound B^7^		X				
Serum human chorionic gonadotropin (hCG)		X				
ECG		X				X
Blood test, urine analysis, stool test (including occult blood)		X				X
Liver/kidney function^8^		X				X
Signed informed consent		X				
Inclusion/exclusion criteria verification			X			
Primary outcome measure	GM^11^ (metagenomics)	X		X	X	X
Secondary outcome measures	RDQ	X	X	X	X	X
	GSRS		X	X	X	X
	Faecal metabolomics^11^	X		X	X	X
	BMI ^9^		X	X	X	X
	LA grade	X				X
Safety measures	AEs			X	X	X
	SAEs			X	X	X
Compliance verification			X	X	X	
Concomitant medications		X	X	X	X	

^1^Visit window: 0 days for visit 1; ± 2 days for visits 2, 3, and 4

^2^Medical history: current and past illnesses, including peptic ulcer, gastritis, oesophagitis, cardiovascular and cerebrovascular diseases, cancer, and mental illness

^3^Medication history: PPI, histamine H2 antagonists, antibiotics, probiotics, prokinetics, gastric mucosal protectors, and other drugs for gastro-oesophageal reflux (including herbs)

^4^Surgical history: gastrointestinal surgeries, including gastro-oesophageal and duodenal surgeries

^5^Performance of gastroscopy in domestic tertiary or higher hospitals in the past 3 months

^6^Gastroscopy at visit 4, LA grades at visit 0 and visit 4 referring to patients with oesophagitis (LA-A, LA-B or LA-C)

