### To minimize confounding interventions

 Prohibited treatments during the study. Probiotics, prebiotics, and foods containing probiotics (such as yogurt) other than those used in this study; Drugs for gastro-oesophageal reflux, such as acid inhibitors, antacids, gastric mucosal protectors, prokinetics, and equivalent drugs [19, 20] (see Additional file 1: Appendix 4) other than the study drug; Antibiotics and probiotics should be taken 2 h apart; Participants will be instructed to avoid spicy foods and to abstain from smoking or drinking during the study.

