### Volunteer compliance monitoring

For the initial treatment (weeks 1–8), the sample package will include rabeprazole and probiotics or rabeprazole and the probiotic placebo; for the maintenance treatment (weeks 9–12), the sample package will include probiotics or the probiotic placebo. After the start of the study, the volunteers will receive a sample package at each monthly visit (package 1 at visit 1, package 2 at visit 2, and package 3 at visit 3) and will be required to return the package at the next visit such that the remaining rabeprazole, probiotics, or probiotic placebo doses can be counted to calculate the compliance level based on the equation below. Compliance ≥ 80% indicates good compliance.

Compliance = [actual amount taken (packets)]/[(amount prescribed (packets)] × 100%

To improve compliance, the study staff will use push messages via a WeChat group established for this study to remind the volunteers to take the sample as scheduled. All volunteers who complete the follow-up will receive 100 yuan as compensation. Moreover, rabeprazole will be provided at no cost during the study.

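### The per-protocol datasets are defined by packet count alone, so they ignore prohibited treatments and also label poor compliers as per protocol

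*Protocol article*

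**What the plan says.** All of this is in the protocol article.

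- **Order of analyses** (Statistical analysis): "First, the intention-to-treat (ITT) analysis will be conducted between the two groups". After that, "per-protocol (PP) analysis will be conducted in the four-subgroup datasets according to compliance"; the strata are 100%, ≥ 80%, 60–80% and < 60%. The stated purpose is "to validate the robustness of the results".
- **Compliance** (Volunteer compliance monitoring): a percentage from the count of returned packs, "Compliance = [actual amount taken (packets)]/[(amount prescribed (packets)] × 100". The same section sets the cut-off: "Compliance ≥ 80% indicates good compliance".
- **Prohibited treatments** (To minimize confounding interventions): "Probiotics, prebiotics, and foods containing probiotics (such as yogurt) other than those used in this study", and also "Drugs for gastro-oesophageal reflux, such as acid inhibitors, antacids, gastric mucosal protectors, prokinetics, and equivalent drugs" apart from the study drug.
- **Recording** (Table 1, under Volunteer recruitment): there is a row for "Concomitant medications". No row for diet is listed.

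No section says what a breach of the prohibited-treatment list does to a patient's place in the analysis datasets.

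**The concern.** A per-protocol analysis is useful as a check on ITT because it removes patients whose conduct blurs the comparison. Here the only sorting variable is how much of the supplied product was taken. That measures dose adherence, and it fails as a per-protocol rule in two ways.

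First, it lets breaches through. The intervention is a probiotic and the primary outcome is the gut microbiome. The breach that matters most, a control patient taking another probiotic, leaves the packet count unchanged. A patient who takes a barred acid suppressant in weeks 9–12, after rabeprazole has ended, is likewise unaffected in the count. The Background section itself ranks PPIs next to antimicrobials for their effect on the microbiota, so such use could disturb the week-12 sample as well as the week-12 symptom scores.

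Second, it puts the per-protocol label on the 60–80% and < 60% strata, although the protocol treats 80% as the threshold for good compliance. The 100% stratum is also contained in the ≥ 80% one, so the four datasets do not form a partition.

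At stake is the meaning of the robustness check. If ITT and these datasets agree, a reader may conclude that protocol breaches did not matter, yet both analyses kept the same patients.

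**Working it through.** **Step 1. Set the rules side by side.** Take a placebo patient with 100% of packets taken who also uses a commercial probiotic throughout.

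- Prohibited-treatment rule: breached.
- Compliance formula: 100%, because only supplied packets enter the ratio.
- Dataset: 100%, and hence also ≥ 80%.

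Now take a patient with 50% of packets taken and no breach. Compliance is below the protocol's own cut-off, but the patient is in the < 60% dataset, which the article also calls per protocol.

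**Step 2. Reproduce the plan's figure.** The Sample size section gives a Chao1 difference of 145, SD 230, α = 0.025 and β = 0.20, and states 47.9 per group.

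n per group = 2 × [SD × (z_α + z_β) / difference]²

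- Two-sided 0.025: 2 × [230 × (2.2414 + 0.8416) / 145]² = 47.83, which matches the stated 47.9.
- One-sided 0.025 (equal to two-sided 0.05): 2 × [230 × (1.9600 + 0.8416) / 145]² = 39.5, which does not match.

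No stated figure is wrong on this point. The Statistical analysis section tests at 0.05, so both levels are shown below.

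**Step 3. Illustrate the effect of outside probiotics in controls.** With 60 per group and 20% loss, 60 × 0.8 = 48 per arm are evaluable.

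Assumption, not in the documents: a share q of controls takes an outside product that removes their whole contrast with the probiotic arm.

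- Expected difference = 145 × (1 − q)
- SE = 230 × √(2/48) = 46.95
- Power = Φ(difference / SE − critical value), with critical value 1.960 (two-sided 0.05) or 2.241 (two-sided 0.025)

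Example, q = 10%: 130.5 / 46.95 = 2.780. Power is Φ(0.820) = 79% at 0.05 and Φ(0.538) = 70% at 0.025.

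If those controls are excluded instead, the difference stays at 145, the control arm becomes 48 × (1 − q), and SE = 230 × √(1/48 + 1/[48(1 − q)]). This further assumes that the excluded patients do not differ in prognosis from the rest.

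| q | Difference if kept | Power if kept, 0.05 / 0.025 | Controls left if excluded | Power if excluded, 0.05 / 0.025 |
|---|---|---|---|---|
| 0% | 145 | 87% / 80% | 48 | 87% / 80% |
| 5% | 137.8 | 84% / 76% | 45.6 | 86% / 79% |
| 10% | 130.5 | 79% / 70% | 43.2 | 85% / 78% |
| 20% | 116 | 70% / 59% | 38.4 | 83% / 75% |

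**Step 4. Acid suppressants.** No calculation is possible. The documents give neither a rate of use nor a direction of bias.

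**The case against.** The strongest objection is that this is an omission of a kind normally settled in the SAP. The prohibited-treatment list is a rule of conduct and defines no analysis set. A list of deviations that lead to exclusion is usually drawn up in the SAP or at a blinded data review, and the SAP is not shown. The article does not say that patients who breach the list are kept.

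Part of this stands. A reader might infer that two sections contradict each other on who is per protocol, or that the sponsor has decided to retain such patients. The documents support neither reading: one section governs conduct, the other sorts patients, and nothing connects them. What does not stand is the idea that the definition was left open. The article gives a complete list of datasets, their single criterion and their purpose. A rule that is stated can be judged as stated.

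Four further objections have force:

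- The contamination rates are assumed, and complete loss of contrast is an upper bound for something like yogurt. At 5% the loss of power is small. At two-sided 0.05, 10% contamination leaves 79%, about the planned 80%.
- The power figures describe the whole trial with 48 per arm. No per-protocol dataset has been sized.
- The Background figure of 54.1% with persistent symptoms among PPI takers may tempt a reader as an estimate of relapse into barred drugs. It comes from a survey of American participants and says nothing about drug use after withdrawal in this trial.
- It is tempting to say that acid suppressants also dilute the effect. Narrowing follows for outside probiotics in controls. For acid suppressants the bias could go either way.

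**Conclusion.** The point holds, limited to the per-protocol definition that the article states. Membership depends on packet count alone. Breaches of the prohibited-treatment list are invisible to it, and two of the four datasets fall below the protocol's own compliance cut-off. The robustness check therefore cannot detect contamination by outside probiotics or other reflux drugs.

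The size is unknown, because it depends on a contamination rate that the documents do not give. Under the assumption of full loss of contrast in 5–20% of controls, power at two-sided 0.05 falls from 87% to between 84% and 70% (at 0.025, from 80% to between 76% and 59%). A lower rate or a weaker outside product gives less.

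It would be wrong to infer that the main result is compromised by this rule: ITT is analysed first and does not depend on it. The defect is in a supporting analysis and should be corrected before unblinding.

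**What to change.** Keep ITT as the first analysis, unchanged. Replace the four per-protocol datasets with one, fixed before unblinding. Suggested text: *The per-protocol set for each assessment comprises participants with compliance of at least 80% and no record, before that assessment, of a probiotic, prebiotic or reflux treatment that the protocol prohibits. Exclusions are decided under blinding and reported by arm with reasons. Results by compliance stratum are descriptive.*

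Two points of data collection need confirming:

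- That concomitant medication is recorded through visit 4. The row in Table 1, as it can be read here, has no mark at week 12, but the table may be broken.
- That participants are asked about probiotic products and foods, since Table 1 lists no diet record. Without such a question the yogurt part of the rule cannot be applied.

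The cost is a short change to the analysis section, a blinded review of the records, possibly one added question at visits, and a somewhat smaller set. There is also a risk of selection: reflux-drug use may be driven by symptoms that arise after randomisation and that treatment may affect, so the patients who remain need not be comparable between arms. The per-protocol result should therefore stay supportive. A worst-rank analysis of the week-12 symptom scores is not required.

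### Two of the four compliance sets called per-protocol are non-adherent by the protocol's own 80% rule, none is named as the main set, and Table 1 conflicts with the text on the visit 4 count

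*Protocol article*

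**What the plan says.** **Analysis sets.** The Statistical analysis section puts the ITT comparison first. It then states that "per-protocol (PP) analysis will be conducted in the four-subgroup datasets according to compliance", with limits of 100%, ≥80%, 60–80% and <60%. The stated purpose is "to validate the robustness of the results". The tests that follow in that section are applied to these datasets without ranking them.

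**Adherence rule.** The section Volunteer compliance monitoring says that a value of at least 80% "indicates good compliance". Compliance is the number of packets taken divided by the number prescribed.

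**When packets are counted.** The same section dispenses "package 1 at visit 1, package 2 at visit 2, and package 3 at visit 3". Participants "will be required to return the package at the next visit such that the remaining rabeprazole, probiotics, or probiotic placebo doses can be counted". The section Intervention strength and management also collects all leftover product and empty packaging when the study ends.

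**Schedule.** In Table 1 (section Volunteer recruitment), the row "Compliance verification" has marks at visits 1, 2 and 3. The visit 4 (week 12) cell is blank.

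**The concern.** A per-protocol analysis supports an ITT result by asking whether the conclusion holds among participants who took the treatment as planned. Two of the four sets consist, by the protocol's own threshold, of participants who did not. If the probiotic works, its effect should weaken at low compliance. Disagreement with ITT in those sets would then not count against the result, and agreement would not confirm it.

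Because no set is designated as the main one, up to four results could be called the per-protocol result, and the plan does not say which one counts.

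The Table 1 point matters because every set is built on the compliance figure. The week-12 Chao1 index drives the sample size, and weeks 9–12 are the four weeks just before that measurement. A schedule that omits the count for those weeks would put participants in the wrong set.

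**Working it through.** **1. The sets against the 80% rule**

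| Set labelled per-protocol | Meets the ≥80% rule? | Relation to other sets |
|---|---|---|
| 100% | yes | nested inside ≥80% |
| ≥80% | yes | contains 100%; shares the value 80% with 60–80% |
| 60–80% | no, except at exactly 80% | shares the value 80% with ≥80% |
| <60% | no | disjoint from all others |

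Four sets make six pairs. One pair is nested, one shares a single boundary value, and four are disjoint.

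**2. How informative the sets could be**

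Inputs from the Sample size section: Chao1 difference 145, SD 230, α = 0.025, β = 0.20, 60 recruited per group.

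The plan's own figure first: n per group = 2 × (z₁₋α/₂ + z₁₋β)² × (SD/difference)². With α = 0.025 two-sided this gives 47.83, against 47.9 stated, so the baseline reproduces. (Read as one-sided, 0.025 would give 39.5.)

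Power in a set of m per arm, by the normal approximation at the two-sided 0.05 of the Statistical analysis section: Φ(145 / (230 × √(2/m)) − 1.96), plus a negligible opposite tail. The planned tests are rank-based, so this is a guide only. The documents do not give set sizes; every m below is an assumption.

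| m per arm (assumed) | 3 | 6 | 9 | 12 | 18 | 30 | 36 | 42 | 48 |
|---|---|---|---|---|---|---|---|---|---|
| Power | 12% | 19% | 27% | 34% | 47% | 69% | 76% | 82% | 87% |

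A low-compliance band of 3 to 18 per arm has power of 12% to 47%. A ≥80% set of 30 to 48 per arm has 69% to 87%.

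**3. Table 1 against the text**

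- Package 1 is handed out at visit 1, so there is nothing to count then; Table 1 marks compliance at that visit.
- Package 3 is handed out at visit 3 and returned at the next visit, which is visit 4; Table 1 has no mark there.
- The column reading fits the other rows of the table: adverse events fall at visits 2 to 4 and GSRS at visits 1 to 4. It still rests on cell positions in extracted text and should be checked against the published table.

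**4. What follows only if Table 1 were followed**

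Weeks 9–12 are 28 of 84 days, and 28/84 = 33%. Let c be probiotic or placebo compliance to week 8. With an equal daily amount throughout, true 12-week compliance lies between 56c/84 and (56c + 28)/84:

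- c = 100%: 66.7% to 100%, which spans the 60–80%, ≥80% and 100% sets.
- c = 90%: 60.0% to 93.3%.
- c = 80%: 53.3% to 86.7%.

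A participant with c = 100% needs (0.8 × 84 − 56)/28 = 40% compliance in weeks 9–12 to reach 80% overall. At 30% in those weeks, the true value is (56 × 1.0 + 28 × 0.3)/84 = 76.7%. That participant would be scored 100% if package 3 were left out of both parts of the ratio.

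**The case against.** ITT leads, all four sets are prespecified, and the ≥80% set matches the protocol's definition of good compliance. Using 100% and ≥80% as two adherence thresholds is ordinary sensitivity practice. Nothing says that the most favourable set will be reported. All of this stands. A reader might infer that the per-protocol plan as a whole cannot serve as a robustness check, but the ≥80% set is a conventional one and can. A reader might also take all four sets to overlap, but only two of the six pairs share any values.

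On the schedule, a reader might conclude that the week-12 count is missing from the plan. The documents do not support that: the text provides for return and counting at visit 4, and leftover product is collected at study end. The concomitant medication row also lacks a visit 4 mark, so a slip of one column is a plausible explanation; the marks also coincide with the dispensing visits. What remains is a conflict between one table row and explicit text.

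Finally, the sets are formed on compliance after randomisation, and the Secondary outcome section expects that compliance may differ between groups because of adverse events. That is a limitation of any per-protocol set, including a single ≥80% set, so it is not a specific argument against the four-set scheme.

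None of this answers the labelling problem. The text assigns the per-protocol name and the validating role to two sets that fail its own adherence rule, and it does not say which set is the main one.

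**Conclusion.** The point holds as a labelling and specification fault in a secondary analysis, together with an internal conflict over one schedule row. The <60% set, and the 60–80% set apart from exactly 80%, are non-adherent by the protocol's rule and cannot validate the ITT result. Exactly 80% is classified twice, and no main set is designated. This part follows from the text alone.

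The power figures for small bands depend on assumed set sizes. The 33% uncounted share, and the 66.7% to 100% range, apply only if staff follow Table 1 instead of the text, and only if the extracted column positions are right. The ITT analysis is unaffected, and the ≥80% set remains a sound robustness check once it is named as such.

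**What to change.** 1. Name the ≥80% set as the single per-protocol set, with compliance calculated by the existing formula over weeks 1–12.
2. Report any other compliance bands as exploratory, with non-overlapping limits: ≥80%, 60 to <80%, and <60%. Do not call the two lower bands per-protocol.
3. Check the compliance row against the published Table 1 and reconcile it with Volunteer compliance monitoring, so that the visit 4 count of package 3 is included.

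The cost is a few words in the Statistical analysis section and one table row. No extra visit or procedure is needed, because return of the third package at visit 4 is already planned.
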